# Heat and Acupuncture to Manage Osteoarthritis of the Knee (HARMOKnee): Protocol for an Effectiveness-Implementation Hybrid Randomized Controlled Trial

**DOI:** 10.2196/54352

**Published:** 2024-04-03

**Keywords:** knee osteoarthritis, acupuncture, heat therapy, effectiveness-implementation hybrid study, randomized controlled trial, RCT

## Abstract

**Background:**

Knee osteoarthritis (KOA) is one of most prevalent and fastest-growing causes of pain, impaired mobility, and poor quality of life in the rapidly aging population worldwide. There is a lack of high-quality evidence on the efficacy of traditional Chinese medicine (TCM), particularly acupuncture, and a lack of KOA practice guidelines that are tailored to unique population demographics and tropical climates.

**Objective:**

Our HARMOKnee (Heat and Acupuncture to Manage Osteoarthritis of the Knee) trial aims to address these gaps by evaluating the short- and medium-term clinical and cost-effectiveness of acupuncture with heat therapy in addition to standard care, compared to standard care alone. Through a robust process and economic evaluation, we aim to inform evidence-based practice for patients with KOA to facilitate the large-scale implementation of a comprehensive and holistic model of care that harmonizes elements of Western medicine and TCM. We hypothesize that acupuncture with heat therapy as an adjunct to standard care is clinically more effective than standard care alone.

**Methods:**

A multicenter, pragmatic, parallel-arm, single-blinded, effectiveness-implementation hybrid randomized controlled trial will be conducted. We intend to recruit 100 patients with KOA randomized to either the control arm (standard care only) or intervention arm (acupuncture with heat therapy, in addition to standard care). The inclusion criteria are being a community ambulator and having primary KOA, excluding patients with secondary arthritis or previous knee replacements. The primary outcome measure is the Knee Osteoarthritis Outcome Score at 6 weeks. Secondary outcome measures include psychological, physical, quality of life, satisfaction, and global outcome measures at 6, 12, and 26 weeks. A mixed method approach through an embedded process evaluation will facilitate large-scale implementation. An economic evaluation will be performed to assess financial sustainability.

**Results:**

Patient enrollment has been ongoing since August 2022. The recruitment process is anticipated to conclude by July 2024, and the findings will be analyzed and publicized as they are obtained. As of November 6, 2023, our patient enrollment stands at 65 individuals.

**Conclusions:**

The findings of our HARMOKnee study will contribute substantial evidence to the current body of literature regarding the effectiveness of acupuncture treatment for KOA. Additionally, we aim to facilitate the creation of standardized national guidelines for evidence-based practice that are specifically tailored to our unique population demographics. Furthermore, we seek to promote the adoption and integration of acupuncture and heat therapy into existing treatment models.

**Trial Registration:**

ClinicalTrials.gov NCT05507619; https://clinicaltrials.gov/study/NCT05507619

**International Registered Report Identifier (IRRID):**

DERR1-10.2196/54352

## Introduction

Knee osteoarthritis (KOA) is an age-related degeneration representing “wear and tear” of the knee joint, and it is one of the most prevalent and fast-growing causes of pain, impaired mobility, and poor quality of life (QOL) in the rapidly aging population worldwide [1]. The 2019 Global Burden of Disease Study reported that the knee is the joint most frequently affected by osteoarthritis, with a prevalence of approximately 365 million, followed by the hand and the hip [2].

Acupuncture is the most prevalent form of traditional medicine practice, with 183 of 202 (90.5%) surveyed countries recognizing its use, as reported by the World Federation of Acupuncture-Moxibustion Societies [3]. A bibliometric analysis reported that of 2189 positive recommendations for the use of acupuncture, about 68% were associated with 107 pain indications [4].

A review of 10 randomized controlled trials (RCTs) concluded that acupuncture is an effective treatment for KOA-related pain and physical dysfunction [5]. However, major updated clinical guidelines from the American Academy of Orthopaedic Surgeons, Joint Surgery Branch of the Chinese Orthopaedic Association, American College of Rheumatology/Arthritis Foundation, and others still consider acupuncture treatment to be insufficient, limited, conditional, or unrecommended for KOA [6]. A review highlighted the lack of evidence supporting the efficacy and cost-effectiveness of acupuncture in osteoarthritis due to poor methodological quality, significant heterogeneity, inadequate reporting of acupuncture treatment details, small sample sizes, and high placebo responses in studies [7].

The primary aim of our study is to evaluate the short- and medium-term clinical effectiveness of acupuncture, part of traditional Chinese medicine (TCM), with far-infrared heat therapy in addition to standard care, compared to standard care alone. The secondary aims include (1) performing a process evaluation to understand the context and identify mechanisms of impact that will inform large-scale implementation of the intervention and (2) performing an economic evaluation to assess the cost-effectiveness of the intervention. We hypothesize that acupuncture with heat therapy as an adjunct to standard care is clinically more effective than standard care alone.

## Methods

### Design

The study is an effectiveness-implementation hybrid trial, which combines effectiveness and implementation components [8,9]. This will be a type 1 hybrid trial where the emphasis and primary aim is to evaluate the effectiveness of acupuncture with far-infrared heat therapy as an adjunct to standard care through a pragmatic RCT under real-world conditions, and its secondary aim is to understand the context of implementation through a mixed-method, process-oriented approach. The pragmatic nature of the study was guided by the Pragmatic Explanatory Continuum Indicator Summary (PRECIS-2) tool [10].

The study will be conducted as a multicenter, pragmatic, parallel-arm, single-blinded RCT using a mixed method approach comparing the clinical effectiveness of acupuncture with far-infrared heat therapy as an adjunct to standard care and standard care alone. The Standard Protocol Items: Recommendations for Interventional Trials (SPIRIT) [11] and the Osteoarthritis Research Society International (OARSI) clinical trial recommendation on the design and conduct of clinical trials for KOA [12] guided the development of the trial protocol. To ensure clear reporting of acupuncture treatment details, Standards for Reporting Interventions in Clinical Trials of Acupuncture (STRICTA) reporting guidelines [13] will also be followed. The findings of the trial will be reported according to the Consolidated Standards of Reporting Trials (CONSORT) 2010 [14] guidelines for reporting parallel-group randomized trials. The study will use an explanatory sequential mixed method design where the qualitative data from interviews will be used to interpret and provide context for the quantitative results.

### Participants

We will recruit patients based on the eligibility criteria outlined in Textbox 1.

Eligibility criteria.
**Inclusion criteria**
National Institute of Health and Care Excellence (NICE) clinical criteria for knee osteoarthritis (KOA) [5]:Being aged 45 years or olderHaving activity-related joint painHaving either no morning joint-related stiffness or morning stiffness that lasts no longer than 30 minutesBeing a community ambulator with or without walking aid
**Exclusion criteria**
Alternative diagnosis to KOA, such as referred pain from the spine or hipOther forms of arthritis, such as inflammatory arthritisInability to comply with study protocol (eg, due to dementia)Previous knee arthroplastyBeing a wheelchair userMedical conditions that would medically interfere with study involvement, such as decompensated heart failure, stroke, and end-stage renal failureAllergies to metal (needles)

### Components of the Study

The Heat and Acupuncture to Manage Osteoarthritis of the Knee (HARMOKnee) study will have three components: (1) an RCT, (2) an economic evaluation, and (3) a process evaluation.

### Component 1: RCT

This RCT will be administered in accordance with the STRICTA guidelines, an extension of the CONSORT statement designed to enhance the quality of clinical trials of acupuncture [13].

#### Trial Procedure and Recruitment

By using the hospital’s electronic medical records and appointment system, patients who are referred to the orthopedic surgery outpatient clinic at a tertiary hospital in Singapore will be screened based on the eligibility criteria prior to their actual consultation visit. During the clinic visit, potential patients will be invited to participate in the study if they meet all the inclusion and exclusion criteria. A research assistant will share details of the study with patients who are interested. Written informed consent will be obtained for those who subsequently agree to join the trial. The reasons for rejection to participate will be recorded. Each consenting participant will be asked to complete the baseline measures. Patients will then be randomized into the control arm or the intervention arm. Considering previous studies [15,16], patients who have received TCM treatment within 1 week prior to the trial will be subject to a 2-week washout period, counting from their last TCM treatment date. They will be requested to stop any form of acupuncture before beginning the trial. For this group of patients, randomization and baseline measures will be performed after the wash-out period. Participants are allowed to take any analgesics as needed throughout the study duration, and this will be recorded. All medications (prescription and over the counter), vitamin and mineral supplements, and herbs taken by the participant will be documented. Data collection will be done at baseline and weeks 6, 12, and 26. The research assistant will follow up with the participants regularly to ensure study completion. Figures 1 and 2 illustrate the study schedule of enrollment, interventions, and outcome measurements according to the SPIRIT guidelines and the CONSORT flowchart, respectively.

**Figure 1 figure1:**
[figure not shown]
Standard Protocol Items: Recommendations for Interventional Trials (SPIRIT) figure of the study schedule. TCM: traditional Chinese medicine.

**Figure 2 figure2:**
[figure not shown]
Consolidated Standards of Reporting Trials (CONSORT) flowchart of the study.

#### Randomization and Concealment of Allocation

Patients who consent to participate will be randomized in a 1:1 allocation ratio to intervention or standard care using a stratified, permuted, block randomization method (block sizes of 4, 6, and 8). Stratification is based on gender with a female to male ratio of 2:1. The unbalance ratio was based on the World Health Organization’s estimate of the prevalence of symptomatic osteoarthritis for people aged 60 years or older, among whom the prevalence of women is almost double that of men (male vs female: 9.6% vs 18%) [17]. The allocation sequence is generated by an independent statistician a priori using Stata (version 16.1; StataCorp) and will be kept concealed from the study team. Randomization will be done using the REDCap (Research Electronic Data Capture; Vanderbilt University) randomization module based on the allocation sequence; allocation will be locked once assigned. Randomization and intervention allocation will only be performed by the study team after the patient is counselled fully about the study and provides informed consent.

#### Intervention: Acupuncture Plus Heat Therapy and Standard Care

After reviewing international literature and engaging with local TCM experts, this clinical intervention was designed in accordance with local practice. The intervention involves acupuncture with far-infrared heat therapy in addition to standard care, which will be administered by qualified TCM practitioners from Tan Tock Seng Hospital’s Complementary Integrative Medicine Clinic (CIMC) and Singapore Chung Hwa Medical Institution (SCHMI), who have full registration with the Traditional Chinese Medicine Practitioners’ Board and a minimum of 3 years of acupuncture practice. Before the commencement of the trial, all the acupuncturists from the participating institutions will undergo training on acupoint locations and needling methods to ensure standardization of acupuncture techniques in accordance to the acupuncture protocol that was developed by consensus among all the senior acupuncturists participating in this trial. The treatment protocol and rationale are elaborated below.

Our study aims to evaluate the therapeutic effectiveness of acupuncture combined with far-infrared heat therapy in addition to standard care, compared to standard care alone. To achieve this purpose, we have not included sham acupuncture as an inactive control in our study design. There are controversies about the validity of sham acupuncture. A study found that sham acupuncture may produce comparable effects on biomarkers as *verum* acupuncture, which suggests that sham acupuncture, being an inactive intervention akin to a placebo, should be reevaluated [18]. Additionally, heat therapy will yield beneficial outcomes in the treatment, regardless of whether *verum* or sham acupuncture is used.

#### Acupuncture Intervention Rationale

Although the 2007 Singapore Ministry of Health clinical guidelines for KOA recommend electroacupuncture as an adjunct therapy, anecdotal input from our local subject matter experts suggests that some patients are afraid of electrical stimulation and that it is generally less well tolerated due to the pain of electrical stimulation. Studies have also shown that even though electroacupuncture has advantages compared to standard care, acupuncture with heat therapy, a more tolerable option, possesses similar efficacy as electroacupuncture when combined with the usual pharmacotherapies [19]. Therefore, we chose to evaluate acupuncture with heat therapy to establish its clinical effectiveness as an adjunctive therapy in the management of KOA, with long-term implementability a key consideration.

Upon careful review of the evidence-based Guidelines of Clinical Practice with Acupuncture and Moxibustion for KOA [20] and the intervention protocols of several acupuncture RCTs that examined patients with KOA (Multimedia Appendix 1, Figure S1 [10, 21-29]), acupoints that were previously reported to be effective in pain relief and improving knee flexibility were identified.

Guided by international evidence in consultation with the local TCM collaborators, a consensus on a set of proximal and distal acupoints based on TCM meridian differentiation was reached (Multimedia Appendix 1, Figure S2 [30,31]).

#### Acupoint Selection

In total, 14 needle insertions will be made on a fixed set of proximal and distal acupoints for each patient per session (Figure 3).

Distal acupoints will be applied on the opposite elbow [32] to increase the analgesic efficacy according to contralateral collateral needling (缪刺) from *Huang Di Nei Jing* (*Yellow Emperor's Inner Classic* in English). It is a therapy where the right side is acupunctured if the left side is diseased and vice versa; the upper side is acupunctured if the below is diseased and vice versa. Studies have shown that contralateral collateral needling unblocks collaterals and is potentially more effective than conventional acupuncture for some conditions, including hemiplegia following acute ischemic stroke, cervical shoulder pain, insomnia, and KOA [33-35]. From a pragmatic perspective, patients with bilateral knee pain will only receive acupuncture on the most painful knee and the opposite elbow. This practice is supported with evidence that suggests unilateral acupuncture is equally as effective as bilateral acupuncture in increasing function and reducing the pain associated with KOA [36].

**Figure 3 figure3:**
[figure not shown]
Proximal and distal acupoints.

#### Treatment Regimen

The patient will be treated in a supine position with pillows under both knees. After a standard disinfection procedure, a 30 × 40–mm disposable stainless steel acupuncture needle (YangTzeKing Impex S Pte Ltd) will be inserted according to the location defined; the direction of insertion and the safe depth range are specified in Multimedia Appendix 1, Figure S2 [21, 30,31]. Basic manipulations such as lifting and thrusting, twirling, and rotating are applied until the needling sensation (*de-qi*) is obtained. After *de-qi* is obtained, uniform reinforcing-reducing (平补平泻) manipulations are applied. The needles will be retained for 30 minutes (except for weizhong [BL40], where the needle is removed immediately after the needling sensation is obtained), whereupon 2 manipulations will be applied at 10-minute intervals before needle removal. During needle retention, far-infrared heat therapy will be applied at the lateral, medial, and anterior sides of the knee for 10 minutes each for a total of 30 minutes while maintaining a 30-cm safety distance (Figure 4). The treated region will be observed and checked for redness at 10-minute intervals to prevent burn injury. A total of 12 acupuncture sessions will be administered twice a week for 6 weeks in addition to standard care. A minimum of 50% attendance (6 of 12 sessions) is required to qualify as completing the study treatment. There are no make-up sessions should the patient miss the scheduled appointment. Total numbers and dates of attended and missed sessions will be recorded for analysis purposes. The study intervention will be conducted at TTSH, CIMC, or SCHMI. The patients are allowed to indicate their preference for the treatment location at the start of the intervention and must attend at the selected location throughout the 6-week intervention. Each TCM session takes approximately 40 minutes, involving acupuncture and heat therapy. Safety precautions will also be exercised to ensure the safety of the patients. Generally, acupuncture is safe and has a low risk of adverse events [37]. However, since the most common adverse events are subcutaneous hematomas and hemorrhages at the site of needling [37], the TCM practitioner will take extra precaution if patients indicate during informed consent that they are taking antiplatelets or anticoagulants. All adverse events that occur during the treatment will be documented.

**Figure 4 figure4:**
[figure not shown]
Heat therapy applied during acupuncture.

#### Standard Care

Standard care generally constitutes simple lifestyle advice, analgesia, and a referral to the outpatient physiotherapist. The physiotherapist conducts an assessment and recommends a variety of lifestyle modifications and exercise therapy. Any other treatment or the involvement of allied health professionals, such as dieticians, will take place at the discretion of the managing physician. The patients in the standard care group will be discouraged from seeking acupuncture treatment for 6 to 8 weeks after randomization. However, if they do so, it will be noted and accounted for in the analysis.

#### Withdrawal Criteria

The study intervention may be discontinued under the following circumstances: (1) a serious adverse event arises from the intervention, (2) a participant opts for total knee replacement, (3) a participant is unable to continue the study (eg, because of the sudden onset of any medical condition that prohibits continuing the study), and (4) a collaborator withdraws due to unforeseen circumstances. The participants may also withdraw voluntarily from the study intervention for any reason.

#### Outcome Measures

The choice of outcome measures is based on the OARSI guidelines for lifestyle diet and exercise clinical trials in osteoarthritis [38]. The recommended core outcomes include pain, physical function, and global patient assessment. Additional outcomes include health-related QOL and global physician assessment. Outcome measures will be collected at baseline (pretreatment), week 6, week 12, and week 26. The primary end point in this study is the Knee Osteoarthritis Outcome Score (KOOS-12) at week 6. KOOS-12 is a specialized tool designed to evaluate patients’ knee condition, and it assesses the short- and long-term effects of knee injuries [39]. It reduces respondent burden by 70% from the original KOOS while providing scale scores for knee-specific pain, function, and QOL, along with a summary measure of overall knee impact [40]. The KOOS score has been validated in Singapore [39,41].

Baseline measures such as demographics, socioeconomic status, medical comorbidities, knee symptoms, radiographic severity, height, and weight will be collected.

Additionally, after considering the progression and severity of KOA as defined in TCM clinical guidelines published in China (Multimedia Appendix 1, Figure S3), 2 evaluation forms have been designed. The Knee Osteoarthritis TCM Evaluation Form (Multimedia Appendix 1, Figure S4) was specifically created to integrate the KOOS-12 knee survey with questions based on TCM syndrome differentiation for KOA. This will enable the investigators to assess the efficacy of the treatment by analyzing syndrome differentiation. This form will be administered at week 1 (start of treatment, before the first acupuncture session), week 4 (midtreatment, before the seventh acupuncture session) and week 6 (end of treatment, after the 12th or last acupuncture session). The Knee Osteoarthritis Visual Analog Scale and Range of Motion Evaluation Form (Multimedia Appendix 1, Figure S5) will be administered before and after each of the 12 biweekly acupuncture sessions over 6 weeks.

Clinical data (glycated hemoglobin, blood pressure, and other chronic disease parameters) and operational and cost data (health care use) will also be obtained through the health care administrative databases for economic evaluation.

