#### Outcome Assessment and Blinding

Except for the TCM evaluation forms (Multimedia Appendix 1, Figures S4 and S5), the remaining outcome measures will be measured by blinded outcome assessors. All outcome assessors will receive training prior to study initiation to ensure good inter- and intraobserver reliability, particularly for the functional performance testing. Patients will be instructed not to reveal their allocation to the outcome assessors. Outcome assessment will be conducted at the TTSH physiotherapy clinic. Unblinding will be carefully considered and justified in each case of medical emergency or clinical treatment decisions that require the intervention to be known, following the study protocol and ethical guidelines.

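### The session-based TCM form cannot show efficacy by syndrome: as described it gives only an uncontrolled, unblinded before-after change in the acupuncture arm

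*Protocol article*

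**What the plan says.** The relevant statements are in the protocol article, under Outcome Measures and under Outcome Assessment and Blinding.

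- **Content.** The TCM Evaluation Form "was specifically created to integrate the KOOS-12 knee survey with questions based on TCM syndrome differentiation for KOA".
- **Purpose.** "This will enable the investigators to assess the efficacy of the treatment by analyzing syndrome differentiation".
- **Timing.** "This form will be administered at week 1 (start of treatment, before the first acupuncture session), week 4 (midtreatment, before the seventh acupuncture session"), and then "week 6 (end of treatment, after the 12th or last acupuncture session"). The companion VAS and range-of-motion form is completed before and after each of the 12 sessions.
- **Blinding.** "Except for the TCM evaluation forms (Multimedia Appendix 1, Figures S4 and S5), the remaining outcome measures will be measured by blinded outcome assessors".
- **Primary end point.** "The primary end point in this study is the Knee Osteoarthritis Outcome Score (KOOS-12) at week 6".
- **Arms.** The abstract describes patients as "randomized to either the control arm (standard care only) or intervention arm (acupuncture with heat therapy, in addition to standard care"). Under Standard Care, the control group is also discouraged from seeking acupuncture for 6 to 8 weeks.

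The baseline measures listed under Outcome Measures do not name TCM syndrome. No other source of syndrome data is described.

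**The concern.** The article defines effectiveness as a contrast with standard care alone, in the Objective, the Introduction and the rationale for having no sham arm. A form whose every time point is an acupuncture session supplies no such contrast. A before-after change on it would be read as efficacy although it has no comparator and is not assessed blind.

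What is at stake is a secondary conclusion. The Discussion treats the local syndrome mix (51% of one type, against 4.2% in China) as a reason why existing guidelines may not fit. A reported improvement by syndrome, labelled as efficacy, could easily be taken up in that debate with more weight than one-arm data can bear.

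**Working it through.** **1. Is there a control measurement?** The form's time points are before session 1, before session 7 and after session 12 or the last one. The control arm receives standard care only, so none of these occasions exists for it. The article describes no other administration of the form.

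**2. What the form then estimates.** For syndrome *s*, let τ(s) be the effect of adding acupuncture with heat, and c(s) the mean change the same patients would have had on standard care alone. Then

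- mean change on the form in the intervention arm = τ(s) + c(s).

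c(s) contains natural course, regression to the mean, and the effect of the analgesia, advice and physiotherapy that both arms may receive. Without controls classified by syndrome, c(s) cannot be removed. Comparing two syndromes within the arm does not help:

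- difference in change = [τ(1) − τ(2)] + [c(1) − c(2)],

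so a syndrome with a better prognosis would look like one that responds better.

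**3. Size of the overstatement.** It equals c(s), which the article does not give. Purely as an assumption, a standard-care change of 3 to 8 points would be 30% to 80% of the 10-point target difference (3/10 and 8/10). The conclusion does not depend on this range.

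**4. Which week-6 KOOS-12 is primary?** Outcome Measures places the outcome measures at baseline and weeks 6, 12 and 26. The blinding section names the TCM forms as the exception and says that "the remaining outcome measures will be measured by blinded outcome assessors". Read together, the primary value is the one from the blinded visit. The article does not say explicitly that a KOOS-12 value from the session form is kept out.

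**5. What recording syndrome in both arms could still deliver.**

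Inputs: 10-point difference, SD 14, 90% power, two-sided 0.05, 20% drop-out, total 100 (Sample Size Calculation); 65 enrolled by November 6, 2023 (Results).

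- The plan's own figure: 2 × (1.960 + 1.282)² × 14² / 10² = 41.2, rounded up to 42. The stated n=42 reproduces as a number per arm.
- Patients remaining after that date: 100 − 65 = 35 at most. After 20% drop-out: 35 × 0.8 = 28, or 14 per arm.
- Assuming two syndrome groups of about equal size (the commonest local type is 51%): about 7 per cell.
- SE of the treatment-by-syndrome interaction: 14 × √(4/7) = 10.6 points.
- Detectable with 80% power: 2.80 × 10.6 ≈ 30 points.

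For comparison, had syndrome been recorded in both arms from the start, with 40 analysed per arm (80% of 50), the cells would be 20.4 and 19.6. The SE would be 14 × √(2/20.4 + 2/19.6) = 6.26 and the detectable interaction 2.80 × 6.26 = 17.5 points. Even that is well above the 10-point target.

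**The case against.** The best defence is that this is loose wording about an add-on form. Syndrome efficacy is not a stated aim or hypothesis and is not among the outcome domains in the abstract. The sentence might only mean following syndrome status through treatment. This lowers the weight of the point but does not remove it: on either reading the word efficacy is attached to data with no comparator.

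A second defence is that the SPIRIT figure and Multimedia Appendix 1 are not shown and could schedule the form for controls. That is possible, so the absence of control data is an inference. It is a strong one, since every stated time point is an acupuncture session.

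A reader might infer more than the article supports:

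- *That the primary analysis is compromised, or that one arm has a choice of primary value.* The blinding section already separates the TCM forms from the blinded outcome measures. Only an explicit exclusion is missing.
- *That the second week-6 score is taken in the treatment room or straight after needling and heat.* The article gives neither place nor interval. How fully the form repeats the KOOS-12 items depends on a figure that is not shown.
- *That extra completions of the questionnaire bias the intervention arm.* Nothing in the article supports an effect of that kind. KOOS-12 is in any case answered by patients who know their allocation, so assessor blinding protects even the primary score only in part.
- *That the guideline aim rests on this form.* The Discussion uses syndrome mix as background and does not say that this form will supply the estimates.

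**Conclusion.** The point holds for the efficacy claim. As described, the TCM form supports only an uncontrolled, unblinded before-after description within the intervention arm, and it cannot support efficacy by syndrome. The same limit applies to the VAS and range-of-motion form, which is also tied to sessions and also exempt from blinded assessment.

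The size of the error in any such claim is the unknown standard-care change in each syndrome group. The conclusion rests on the stated timing and blinding, and on the inference that controls do not complete the form. The randomized primary comparison stands. For the week-6 KOOS-12, what remains is a minor clarification.

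**What to change.** 1. **Main change.** Replace the sentence on efficacy by syndrome with wording such as: *The TCM Evaluation Form and the VAS and range-of-motion form are completed in the intervention arm only and without blinding. Their data will be summarized descriptively as within-arm change and will not support conclusions on syndrome-specific efficacy.* If the full protocol does schedule the forms for controls, say so instead and state how the arms will be compared.
2. **Minor clarification.** State that only the KOOS-12 from the blinded week-6 visit enters the primary analysis and that session-form KOOS-12 values do not.
3. **Optional.** For patients still to be enrolled, record syndrome at baseline in both arms before randomization and report a treatment-by-syndrome interaction on the blinded KOOS-12 as exploratory. It would be very imprecise: 35 was the most that could remain in November 2023, fewer remain as recruitment proceeds, and the detectable interaction is already about 30 points at that number.

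Items 1 and 2 cost a few sentences and cover all patients; the price is giving up the syndrome efficacy claim. Item 3 costs a few baseline questions and returns little.
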